#### Sample size calculation

2.6.3

Based on the primary objective of the study, a sample size calculation was performed using G*Power software. The estimation assumes a 20% relative reduction in the rate of hospital admissions (including emergency department visits and hospitalizations) in the intervention group compared to the control group. Using a two-sided alpha of 0.05 and a statistical power (1–*β*) of 85%, the required sample size was calculated to be 186 participants. To account for a potential 10% dropout rate, the total planned enrollment is set at 205 patients with chronic HF. However, the study team elected to enroll 300 patients to further strengthen the statistical robustness of the analysis. This larger planned sample provides several advantages:
it compensates for potential attrition, incomplete adherence, or missing data;it increases the precision of effect estimates in a clinically heterogeneous HF population;it enhances the stability of exploratory subgroup analyses across LVEF phenotypes (HFrEF, HFmrEF, HFpEF);it improves the reliability and generalizability of machine-learning models derived from multimodal wearable data.Thus, while 205 participants represent the minimum requirement based on power analysis, the planned enrollment of 300 patients ensures greater analytical robustness and supports the broader aims of the SMART-CARE project.

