### Outcomes

2.4

Both groups will undergo assessments at baseline, 3 months, and 6 months, including evaluations of functional status, echocardiographic parameters, biochemical markers (e.g., BNP, NT-proBNP, renal function), and quality of life assessed using the Kansas City Cardiomyopathy Questionnaire (KCCQ) (36–39) (Table 2).

**Table 2 T2:** SMART-CARE outcome measures by timepoint.

Outcome type	Outcome measure	Domain	Baseline	3 months	6 months
Primary	Change in Hospital Admissions	Clinical Events			✔
Secondary	Change in Quality of Life (KCCQ Score)	Quality of Life	✔	✔	✔
Secondary	Adverse Effects of CHF Therapy	Safety			✔
Secondary	Change in BNP Levels	Biochemical	✔	✔	✔
Secondary	Change in NT-proBNP Levels	Biochemical	✔	✔	✔
Secondary	Change in Serum Creatinine	Biochemical	✔	✔	✔
Secondary	Change in eGFR	Biochemical	✔	✔	✔
Secondary	Change in Serum Sodium	Biochemical	✔	✔	✔
Secondary	Change in Serum Potassium	Biochemical	✔	✔	✔
Secondary	Change in Serum Chloride	Biochemical	✔	✔	✔
Secondary	Change in HRV	Functional (ECG)	✔	✔	✔
Secondary	Change in Respiratory Rate	Functional (ECG)	✔	✔	✔
Secondary	Change in LVEF	Echocardiographic	✔	✔	✔
Secondary	Change in E/A Ratio	Echocardiographic	✔	✔	✔
Secondary	Change in LV End-Diastolic Volume	Echocardiographic	✔	✔	✔
Secondary	Change in LV End-Systolic Volume	Echocardiographic	✔	✔	✔

CHF, chronic heart failure; KCCQ, Kansas City Cardiomyopathy Questionnaire; BNP, B-type Natriuretic Peptide; NT-proBNP, N-terminal pro-B-type Natriuretic Peptide; eGFR, estimated Glomerular Filtration Rate; HRV, Heart Rate Variability; ECG, Electrocardiogram; LVEF, Left Ventricular Ejection Fraction; E/A Ratio, Early to Late Ventricular Filling Velocity Ratio; LV, left ventricle.

The primary outcome of the SMART-CARE study is the relative reduction (≥20%) in hospital admissions, including emergency department visits and unplanned hospitalizations, over a six-month follow-up period in the intervention group compared to standard care (40). Hospitalization data will be collected prospectively and analysed for frequency, duration, and cause.

Secondary outcomes include:

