#### Primary endpoint analysis

2.6.1

To assess the primary endpoint of the study, Kaplan–Meier survival curves will be constructed to compare the time to first hospitalization between groups. Group differences will be evaluated using the log-rank test. Subsequently, a Cox proportional hazards regression analysis model will be performed to examine the association between the variable “Device Use (Yes vs. No)” and the reduction in hospital admissions. The model will be adjusted for all statistically significant covariates identified through ANOVA between the two groups. To mitigate selection bias resulting from the non-randomized design, propensity score methods will be applied. The propensity score will be estimated using baseline variables including age, sex, LVEF phenotype, NYHA class, major comorbidities (hypertension, atrial fibrillation, diabetes mellitus, COPD/OSA, obesity), prior HF hospitalizations, baseline biomarkers (BNP/NT-proBNP, renal function, electrolytes), and key echocardiographic indices (LVEF, LV volumes). A 1:1 nearest-neighbour matching approach without replacement will be used. Covariate balance between groups will be evaluated using standardized mean differences (SMD), with values <0.10 indicating adequate balance. Results will be expressed as hazard ratios (HR) with corresponding 95% confidence intervals (CI).

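### The stated 186 patients and 85% power do not follow from a 20% relative reduction in admissions unless the control event rate is very high, and 300 patients also fall well short at control risks of 30 to 60%

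*Protocol article*

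**What the plan says.** Section 2.6.3 (Sample size calculation) gives the effect as a relative one: "The estimation assumes a 20% relative reduction in the rate of hospital admissions", with emergency department visits counted. It continues "Using a two-sided alpha of 0.05 and a statistical power" "of 85%, the required sample size was calculated to be 186 participants". Ten per cent dropout takes this to 205, and the team then chose to enrol 300. The section closes by saying that "while 205 participants represent the minimum requirement based on power analysis". It names the software but gives no control-group rate, test or allocation ratio.

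Section 2.4 (Outcomes) uses the same effect: "The primary outcome of the SMART-CARE study is the relative reduction (≥20%) in hospital admissions". Section 2.6.1 (Primary endpoint analysis) will "compare the time to first hospitalization between groups" by Kaplan–Meier curves and the log-rank test, followed by Cox regression with hazard ratios and 95% confidence intervals.

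**The concern.** A 20% relative reduction is a modest effect, and detecting it with 85% power normally takes many hundreds of patients. A total of 186 is possible only if nearly all controls have an event, and the article gives no sign of such a rate. Nor does the number fit the planned time-to-first-event analysis if the 20% is read as a hazard ratio of 0.80.

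The stated power belongs to the primary objective. If it is wrong, a reader of a non-significant result could believe that a 20% reduction had been looked for with at least 85% power and not found, although the study had much less chance of detecting it. The choice of 300 is also presented as a margin above an adequate minimum, and that minimum is not supported.

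**Working it through.** **Inputs.** From section 2.6.3: 20% relative reduction, two-sided alpha 0.05 (z = 1.960), power 85% (z = 1.036), 186 in total, 300 planned. From section 2.6.1: log-rank and Cox on first hospitalization. Assumed: 1:1 allocation (not stated for the calculation; the analysis uses 1:1 matching) and control six-month risks p of 30 to 60%, because the article gives none.

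**Step 1. Try to reproduce 186 with two proportions.** Pooled formula, per group, with p1 = p, p2 = 0.8p and m the mean of the two:

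n = [1.960·√(2m(1−m)) + 1.036·√(p1(1−p1) + p2(1−p2))]² / (p1−p2)²

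At p = 40% (40% v 32%): (1.330 + 0.701)² / 0.08² = 644.9, so 645 per group and 1,290 in total. Setting n = 93 and solving for p gives p = 0.882. So 186 is reproduced only at a control risk of about 88%.

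| Control risk | Total N for 85% power | Power with 186 | Power with 300 (150:150) |
|---|---|---|---|
| 30% | 1,964 | 15% | 21% |
| 40% | 1,290 | 20% | 30% |
| 50% | 886 | 28% | 41% |
| 60% | 618 | 37% | 55% |
| 70% | 424 | 51% | 71% |
| 80% | 280 | 68% | 87% |

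With 270 analysed (300 less 10%), power is 20% at a control risk of 30% and 28% at 40%.

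**Step 2. Try to reproduce 186 with counts.** Poisson rate ratio 0.8, control mean r per six months: n = (1.960+1.036)²·(1 + 1/0.8) / [(ln 0.8)²·r]. With n = 93, r = 8.978 × 2.25 / (0.04979 × 93) = 4.36 admissions per control patient. With 150 per group, 85% power would still need r = 8.978 × 2.25 / (0.04979 × 150) = 2.7. At r = 0.5 and 1.0, power with 300 is 25% and 45%.

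**Step 3. The planned log-rank test, with the 20% as a hazard reduction (HR 0.80).** Events = 4(1.960+1.036)² / (ln 0.8)² = 4 × 8.978 / 0.04979 = 721.3, so 722. A patient supplies at most one first event. If every patient had one, power would be 33% with 186, 36% with 205 and 49% with 300.

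**Step 4. The planned log-rank test, with the 20% as a risk reduction.** Under proportional hazards, HR = ln(1−0.8p) / ln(1−p).

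| Control risk | Power at HR 0.80, 300 patients | Converted HR | Power at converted HR, 300 patients |
|---|---|---|---|
| 30% | 17% | 0.77 | 22% |
| 40% | 22% | 0.755 | 31% |
| 50% | 26% | 0.74 | 43% |
| 60% | 30% | 0.71 | 57% |

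**Step 5. What 300 can detect.** By two proportions at 150:150 with 85% power, the detectable relative reduction is about 48, 40 and 34% at control risks of 30, 40 and 50%.

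**Step 6. Where 186 might come from.** 40% v 20% gives (1.270 + 0.655)² / 0.20² = 92.7, so 93 per group and 186 in total. By symmetry 80% v 60% gives the same. Both are falls of 20 percentage points; in relative terms they are 50% and 25%.

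**The case against.** The best defence is that the control rate is unknown and could be high. Table 1 requires a hospitalization or an outpatient visit with intravenous therapy in the past 12 months, and the outcome counts emergency department visits. The document therefore cannot prove that 88% is wrong. That stands, and it is why the result is given as a range. But the document does not support such a rate either: section 2.1 describes clinically stable patients on optimized therapy, and NYHA class IV is excluded.

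A condensed article may also leave the control rate and test to the full protocol. Their absence is not the charge here. The charge is that a complete result is stated and does not follow from the inputs given with it, except in an extreme case.

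Four stronger readings are tempting, and the document does not bear them out:

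- **That the calculation was really for a fall from 40% to 20%, a 50% relative reduction.** The match is exact but not unique: 80% v 60% fits equally, and so does a one-degree-of-freedom chi-square with w = 0.22 (8.978 / 0.0484 = 185.5, so 186). Absolute points used in place of relative per cent is a possible cause, not a documented one.
- **That 300 patients have 20 to 30% power.** This holds only at some control risks. By two proportions it is 41% at a risk of 50% and 55% at 60%.
- **That the 722 events and the 49% ceiling apply whatever the 20% means.** They apply only if it is a hazard reduction. As a risk reduction, the log-rank figures in step 4 with the converted HR are the relevant ones, and power passes 85% if the control risk is near 80%.
- **That enrolling 300 adds nothing.** It does improve precision and absorb attrition compared with 205, as section 2.6.3 says. What fails is the adequacy of 205.

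A reader may also notice that 186/0.9 is 207, not 205. With 300 enrolled this is immaterial.

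**Conclusion.** The point holds. For a 20% relative reduction at two-sided 0.05 and 85% power, a total of 186 follows only at a control risk of about 88%, or about 4.4 admissions per control patient. At control risks of 30 to 60% the required total is 1,964 down to 618. With 300 analysed 1:1, power is 21 to 55% by two proportions, 22 to 57% by log-rank with the converted HR, and 17 to 30% by log-rank at HR 0.80. Three hundred patients reach 85% only with a control risk near 80% (20% as a risk reduction) or about 2.7 admissions per control patient (Poisson); at HR 0.80 they cannot reach it at all.

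These figures assume equal groups, the listed control risks and, for the converted HR, proportional hazards. Groups formed by patient choice and patients left unmatched by 1:1 matching would tend to lower the power further. The statements of 85% power for a 20% relative reduction and of 205 as the minimum should not stand as written.

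**What to change.** Keep the enrolment of 300 and rewrite section 2.6.3:

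1. State the control rate, test and allocation actually entered in the calculation, and whether the 20% is a relative reduction or an absolute difference in percentage points. If relative, say whether in risk, rate or hazard.
2. Replace the 85% claim with the power for a 20% relative reduction at 300 over a stated range of control risks, using the planned analysis. Alternatively, give the effect detectable with 85% power at 300 (about 48, 40 and 34% relative at control risks of 30, 40 and 50%).
3. Remove the statement that 205 is the minimum requirement from the power analysis.
4. Add that a non-significant result does not exclude a 20% reduction, and that the result will be read from the estimate and its confidence interval, which section 2.6.1 already plans to report.

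The cost is the rewording of one section, with no added patients and no change to conduct. The downside is that the stated power becomes much less favourable.

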#### Handling of missing data and dropouts

2.6.4

Missing data and incomplete follow-up will be handled according to established recommendations for observational cohort studies. For clinical, biochemical, and echocardiographic variables, the pattern and mechanism of missingness will be evaluated. When data are missing at random (MAR), multiple imputation using chained equations (MICE) will be applied to reduce bias and preserve statistical power. In case of non-random missingness, sensitivity analyses will be performed using complete-case analysis and worst-case/best-case scenarios. For time-to-event analyses, dropouts will be treated as censored observations at the last available follow-up. Device adherence will be quantified as the percentage of monitoring days with valid wearable data; predefined thresholds for minimum acceptable adherence will be applied in sensitivity analyses. Per-protocol and intention-to-monitor analyses will be conducted to assess the robustness of the findings with respect to missing data and incomplete device use.

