#### Secondary endpoint analysis

2.6.2

Continuous variables will be presented as mean ± standard deviation (SD) for normally distributed data and as median and interquartile range (IQR) for non-normally distributed data. Categorical variables will be expressed as frequencies and percentages. The normality of distribution will be tested using the Shapiro–Wilk test. For normally distributed continuous variables, comparisons will be made using the paired t-test or one-way repeated measures ANOVA, depending on the situation. For non-normally distributed data, the Wilcoxon Signed-Rank test will be applied. Categorical variables will be compared using the Pearson chi-square test. Given the intrinsic differences in echocardiographic and clinical trajectories between HFrEF and HFpEF patients, all secondary endpoints (including echocardiographic parameters, biomarkers, and functional indices) will also undergo stratified analyses by LVEF phenotype. This approach is intended to avoid the dilution of clinically meaningful changes in subgroups with limited baseline variability, particularly among HFpEF patients. Subgroup analyses based on LVEF phenotype (HFrEF, HFmrEF, HFpEF) will be performed as exploratory analyses. The study is not powered to detect statistically significant differences between these subgroups; therefore, these analyses are intended to be descriptive and hypothesis-generating. To mitigate potential confounding when comparing phenotypes, LVEF category will be included as a covariate in multivariable models, and propensity score techniques will be applied when appropriate. Because echocardiographic parameters show markedly different baseline ranges and variability in HFrEF and HFpEF, echocardiographic secondary outcomes will also be interpreted within each LVEF phenotype. This approach is intended to avoid the dilution of true within-group changes in HFpEF patients, in whom structural parameters often fall within or near the normal range. A two-sided *p*-value < 0.05 will be considered statistically significant for all final analyses.

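### Section 2.6.4 makes multiple imputation depend on a MAR finding that the data cannot give, and lists complete-case analysis as a response to non-random missingness

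*Protocol article*

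**What the plan says.** Section 2.6.4 of the protocol article (Handling of missing data and dropouts) sets a sequence.

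- **Scope:** "For clinical, biochemical, and echocardiographic variables".
- **Diagnosis:** "the pattern and mechanism of missingness will be evaluated".
- **Branch 1:** "When data are missing at random (MAR), multiple imputation using chained equations (MICE) will be applied to reduce bias and preserve statistical power".
- **Branch 2:** "In case of non-random missingness, sensitivity analyses will be performed using complete-case analysis and worst-case/best-case scenarios".
- **Separate rule for the primary analysis:** "For time-to-event analyses, dropouts will be treated as censored observations at the last available follow-up".

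The only figure in the article tied to loss of data is in section 2.6.3: "To account for a potential 10% dropout rate, the total planned enrollment is set at 205 patients with chronic HF".

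**The concern.** The choice between the two branches rests on whether data are MAR or not. That distinction concerns values nobody has seen, so no inspection of the collected data can settle it. The method is therefore left to judgement once the data are in hand.

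The second branch then lists complete-case analysis. That method generally needs data missing completely at random, or missingness explained by covariates in the model. It does not relax MAR towards outcome-dependent missingness.

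This matters because patients join a group by willingness to use the device (section 2.2), and one group has alerts and teleconsultation between visits while the other does not. Missingness could plausibly differ between groups and relate to deterioration. Biomarkers and echocardiographic indices are both secondary outcomes (Table 2) and inputs to the propensity score (section 2.6.1), so the rule touches both uses.

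**Working it through.** **1. The plan's own figure.** Inputs: 186 participants and 10% dropout (section 2.6.3).

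- 186 x 1.10 = 204.6, rounded up to 205. This reproduces the stated figure.
- Dividing instead, 186 / (1 - 0.10) = 206.7, rounded up to 207. With 300 to be enrolled, the gap of 2 has no consequence.

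The article gives no split of dropout by group and nothing on how patients with missing values would differ. The bias therefore cannot be computed from the document, and steps 3 to 5 use assumed values.

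**2. Can the switch be operated?** MAR means that, given what was observed, the chance of being missing does not depend on the unobserved value. Testing this needs the unobserved value. An association between missingness and observed variables rules out missingness completely at random and nothing more. Two readings are possible:

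- *Literal:* MICE is used only under MAR. The other branch then names sensitivity analyses and no main analysis.
- *Generous:* MICE is always the main analysis and branch 2 is an addition. The sensitivity analysis then waits for a diagnosis that cannot be made, and may never be run.

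Both need correction.

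**3. Complete-case bias in a group mean.** With fraction f missing, full mean = (1 - f) x observed mean + f x missing mean. So observed mean - full mean = f x gap, where gap = observed mean - missing mean. Assumed KCCQ inputs:

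| Missing, control | Missing, device | Gap (points) | Bias, control | Bias, device | Bias, device minus control |
|---|---|---|---|---|---|
| 20% | 10% | 10 | +2.0 | +1.0 | -1.0 |
| 20% | 10% | 15 | +3.0 | +1.5 | -1.5 |
| 20% | 10% | 20 | +4.0 | +2.0 | -2.0 |
| 10% | 10% | 15 | +1.5 | +1.5 | 0 |
| 10% | 20% | 15 | +1.5 | +3.0 | +1.5 |

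**4. Width of best/worst-case bounds.** Assume a 0-100 KCCQ scale, 10% missing in each group, and whole-scale extremes. Each group mean can move by 0.10 x 100 = 10 points, so the bounds on the difference span 10 + 10 = 20 points. BNP and NT-proBNP have no natural maximum to use as an extreme.

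**5. Illustrative simulation.** Assumed: 150 per group, true difference 0.30 SD, baseline-outcome correlation 0.5, 1000 runs. Missingness in the device group is driven by a worse baseline value (MAR) or a worse outcome (MNAR); control missingness is unrelated to either.

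| Mechanism | Overall missing | Complete-case, unadjusted | Complete-case, baseline-adjusted |
|---|---|---|---|
| Completely at random | 10% / 20% | 0.30 / 0.31 | 0.30 / 0.31 |
| MAR on baseline | 10% / 20% | 0.37 / 0.43 | 0.30 / 0.30 |
| MNAR on outcome | 10% / 20% | 0.43 / 0.54 | 0.40 / 0.48 |

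Under MNAR the complete-case estimate is off by 0.13 and 0.24 SD unadjusted, and by 0.10 and 0.18 SD adjusted. MICE using the same baseline information would not remove this either, which is why a delta shift is needed. Here the bias favours the device; in the first three rows of step 3 it goes the other way. The direction follows from the assumption made.

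**The case against.** The strongest case for the plan is as follows.

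- **The response is not complete-case alone.** The same sentence adds best/worst-case scenarios, which do bound departures from MAR, and defining their values is ordinary analysis-plan content. This stands. What remains is that they are run only after the untestable diagnosis.
- **Complete-case is labelled a sensitivity analysis,** and it can be unbiased when missingness depends only on modelled covariates. This stands, but that situation is not the non-random one it is listed for.
- **The primary outcome has its own censoring rule,** and the plan adds per-protocol and intention-to-monitor analyses. This stands and limits the reach. A reader might infer that the rule undermines the primary comparison; the text supports only an indirect route through missing covariates.
- **Assessing missingness need not involve looking at group comparisons,** and both groups have the same three scheduled assessments (section 2.1). This stands. Choice made in view of results, and differential missingness, are possibilities that the text leaves open; it does not show either.
- **The KCCQ inputs are assumptions.** KCCQ has its own domain in Table 2 and is not clearly inside the scope wording of section 2.6.4. This stands; the KCCQ figures are illustrations.

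Two further inferences are tempting. One is that MICE would fill in the E/A ratio in patients in atrial fibrillation, or values after death. The article speaks of missing data and says neither; a value that is undefined is not plainly within a missing-data rule. The other is that the complete-case result would look falsely reassuring about benefit. With more missing in controls, step 3 gives bias against the device, so that does not follow.

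**Conclusion.** The point holds in limited form. Section 2.6.4 states a rule that cannot be operated as written, because observed data cannot establish MAR against MNAR. It also lists complete-case analysis as a response to the very situation in which that method is generally biased. This is a stated rule fixed badly; it does not depend on detail left to a fuller document.

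Its reach is mainly the secondary endpoints and the baseline covariates in the propensity score and adjusted models. The KCCQ range in step 3 and the simulated values in step 5 rest wholly on assumed missingness rates, gaps and mechanisms. They show that bias can arise and can take either sign; they are not estimates for this trial. The core argument needs none of these numbers.

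**What to change.** In section 2.6.4:

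1. State that MICE under an assumed MAR mechanism is the main approach regardless of any missingness assessment, with group and the admission indicator in the imputation model. The assessment then describes the missing data and no longer selects the method.
2. Always run a delta-adjusted (tipping-point) sensitivity analysis: shift imputed values by a range of deltas, set separately by group, and report where the conclusion changes.
3. Keep complete-case analysis as a supplementary description only, and stop presenting it as the answer to non-random missingness.

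Cost: revised wording and modest extra programming. No new data are needed and the sample size does not change.
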